**Fig. 1 Fig1:**
[figure not shown]
SPIRIT figure

#### Sample size

The required sample size is determined for the primary endpoint EASI50 at 3 months follow-up. Based on previous research published in the literature incidences of 50% effectiveness for reaching EASI50 using NB-UVB, and of 20–30% using only OTT are to be expected [37–40].

Sample sizes of 134 in both arms achieve 90% power to detect a difference between the group proportions of 20 percentage points. The proportion in the NB-UVB + OTT treatment group is assumed to be 30% under the null hypothesis and 50% under the alternative hypothesis. The assumed proportion in the control group treated with OTT alone is 30%. The test statistic used is the two-sided *Z*-test pooled variance. The significance level of the test is 5%. Interim analyses for early stopping will not be conducted; hence, no correction of the significance level for interim analyses is required. Allowing for a drop-out rate of up to 15%, a total of 316 patients will be recruited.

#### Recruitment

Subjects will be recruited from the patient population of each participating center. Additionally, recruitment will take place via the members of the Dutch Society of Dermatology and Venereology (NVDV) and the Dutch Association for People with Constitutional Eczema (VMCE). The investigators, NVDV members, and the VMCE board will be provided with promotional material that has been reviewed by the medical research ethics committee (MREC). In addition, MREC-evaluated promotional posters and texts will be distributed via NVDV- or VMCE-based media. This includes printed advertisements in magazines and digital promotion via sites/apps such as Facebook, Instagram, and LinkedIn.

### Randomization

Patients who meet eligibility criteria and who have provided written informed consent will be randomly allocated in a 1:1 ratio to either NB-UVB + OTT or OTT alone. To ensure allocation concealment, automated randomization is performed by the investigator using the electronic data management system Castor EDC. Randomization will use random permuted blocks.

### Blinding

During baseline- and follow-up visits, physician-reported outcomes (EASI, vIGA-AD) will be assessed. As these outcomes are subject to investigator bias, the physician outcome assessor will be blinded for treatment allocation. This independent (local) investigator will solely see the patient during the physical examination phase of the study visit. The patient will be instructed to not disclose their allocation outcome to this investigator. However, as NB-UVB may cause redness and tanning of the skin in light skin types, complete blinding of the outcome assessor will not be guaranteed. All other investigators or physicians performing study activities other than assessing EASI and vIGA-AD may be unblinded. The blinded outcome assessor may be unblinded when this is necessary to ensure patient safety.

### Data collection and management

All data is handled confidentially and in accordance with the European General Data Protection Regulation.

During baseline- and follow-up visits, physician-reported outcomes will be assessed by a blinded assessor who will note his/her findings on paper. This source document will be dated, signed, and kept on-site. All other study activities and the registration of physician-reported outcomes into the digital case report form (CRF) will be done by the investigator performing the study visit. Patient-reported outcomes will be entered by the participant into the electronic data management system via an invitation link, during or after every study visit. No biological specimens will be collected.

All patients will be assigned a unique subject identification number. Patients can be identified through a subject identification log and all data kept centrally will therefore be pseudonymized. This key linking patients with their identification number will be in possession of the investigators. Subject identification logs are kept on-site only and will not be shared centrally or with other sites.

Data will be collected in an electronic data management system: Castor Electronic Data Capture, from CIWIT BV, Amsterdam, the Netherlands: www.castoredc.com. Personnel responsible, e.g., data entry, monitoring, data validation, data exporting, and database administration, will have access to the database. Data handling will be described in the standard operating procedures (SOPs). All study documents will be stored securely in an environment only accessible to study team members. Data will be archived according to the local procedures of the sponsor. Data management was designed to adhere to the “FAIR Guiding Principles for scientific data management and stewardship,” aiming to optimize the Findability, Accessibility, Interoperability, and Reuse of digital assets [41].

### Statistical methods

#### Statistical methods for primary and secondary outcomes

The primary outcome measure will be estimated as a relative risk and absolute risk difference with 95% confidence interval and *p*-value. The primary outcome will be analyzed using a generalized linear model with binomial distribution and log-, or identity-link respectively. The primary analysis will be run using the intention-to-treat population. Missing data for the primary outcome is expected to be low, although meaningful drop-out can be expected.

A secondary analysis will be done using the per-protocol population. Exploratory subgroup analyses will be run, e.g., location of receiving NB-UVB (out-patient clinic or at home) and below or above the median EASI score at baseline.

Dichotomous secondary outcomes will be presented as counts, percentages, and relative risks according 95% confidence interval, and *p*-values will be calculated using the chi-square test or Fisher exact test as appropriate. Continuous variables will be presented as means with standard deviation when data distribution is normal. In case of skewed data medians with interquartile ranges will be used for presentation. The mean or median differences between the groups will be calculated with accompanying 95% confidence intervals using Satterthwaite’s or Hodges-Lehmann’s tests. Longitudinal data (repeated measures of, e.g., EASI, POEM, NRS-11, and EQ-5D-5L) will be analyzed using generalized estimating equations and adjusted for baseline values. Time to switching to systemic therapy will be analyzed as a time-to-event outcome using a Kaplan–Meier plot and log-rank test.

Multiple imputation will be used as necessary for secondary analyses and sensitivity analyses. The effects of intercurrent events will be assessed in sensitivity analyses. A detailed statistical analysis plan will be completed before the database lock.

The economic evaluation of NB-UVB as an add-on to OTT compared to OTT alone in this study population will be performed as a cost-utility analysis (CUA) from a societal perspective with the costs per quality-adjusted life year (QALY) as a primary outcome. Health utilities will be derived from the EQ-5D-5L health status profiles using the existing scoring algorithm [42]. The scoring algorithm is based on preferences in the general population for being in a particular health state, using the time trade-off elicitation technique. The health utility score may range from − 0.44 to 1.0, reflecting the worst, respectively, best health states possible. Deceased patients will be assigned a health utility score of 0. QALYs will be calculated as the area under the curve of health utility scores over time. In addition, a cost-effectiveness analysis (CEA) will be done with the costs per patient with a EASI50 as an outcome. The analysis will include the costs of health care (in-patient and out-patient hospital care, institutional care elsewhere, out-of-hospital care like general practitioner, and extramural drugs) and costs of productivity loss resulting from sick leave from work or lowered efficiency while at work. The volume of resources used will be gathered with clinical report forms and with patient questionnaires on medical consumption (iMCQ) and productivity loss (iPCQ) adapted for this study. No interim analyses are planned.

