##### Primary outcome

Percentage of patients with EASI50 (a 50% decrease in EASI) at 3 months follow up (range EASI 0-72) [23, 24].

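### The primary EASI50 model names no baseline covariate and uses links that carry one poorly; a standardised logistic model adjusted for baseline EASI may add a little precision

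*Protocol article*

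**What the plan says.** The primary outcome is "Percentage of patients with EASI50 (a 50% decrease in EASI) at 3 months follow up" (Protocol article, Primary outcome). Under Statistical methods for primary and secondary outcomes, the effect is to be given as a relative risk and a risk difference in the intention-to-treat population, and "The primary outcome will be analyzed using a generalized linear model with binomial distribution and log-, or identity-link respectively". No covariate is listed, and none is ruled out.

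The same section is explicit about adjustment elsewhere: repeated measures such as EASI and POEM "will be analyzed using generalized estimating equations and adjusted for baseline values". It also plans an exploratory subgroup split "below or above the median EASI score at baseline". The Blinding section confirms that the baseline value exists: "During baseline- and follow-up visits, physician-reported outcomes (EASI, vIGA-AD) will be assessed". The inclusion criteria set a minimum EASI of 7, so every randomised patient needs a score at entry.

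The Sample size section rests on an unadjusted comparison of two proportions: "The test statistic used is the two-sided" Z-test with pooled variance. The Randomization section names permuted blocks and no stratification factor. Further detail is deferred: "A detailed statistical analysis plan will be completed before the database lock".

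**The concern.** Adjustment is named for the longitudinal analyses and not for the primary one, and the sample size uses a two-proportion test. The natural reading is therefore that EASI50 will be compared between arms without covariates. If baseline EASI predicts who reaches EASI50, that comparison has a somewhat wider confidence interval than the collected data allow.

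The choice of link makes this more than a blank in a covariate list. With treatment as the only term, log- and identity-link binomial models simply reproduce the two observed proportions and fit without difficulty. Once a continuous covariate enters, neither link keeps fitted risks within 0 to 1, and the fit may not converge. Adding baseline EASI to the model as published could therefore fail, and the estimator would have to be changed late.

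At stake is some precision in the primary estimate and a smooth route to adjustment. The validity of the trial is not at stake.

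**Working it through.** **1. The plan's own figure.** Inputs from Sample size: 50% versus 30%, two-sided 5%, 90% power, 15% drop-out.

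- Pooled Z-test: n = [1.96·√(2·0.4·0.6) + 1.2816·√(0.25 + 0.21)]² / 0.2² = (1.358 + 0.869)² / 0.04 ≈ 124 per arm.
- With continuity correction: (124/4)·[1 + √(1 + 4/(124·0.2))]² ≈ 133.8, so 134 per arm, as stated.
- Drop-out: 134/0.85 = 157.6, so 158 per arm and 316 in total, as stated.

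The section does not mention the continuity correction; using it is conservative. Without it, power at 134 per arm is Φ[(0.2·√134 − 1.358)/0.678] = Φ(1.411) = 92.1%. This is the reference below.

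**2. What adjustment could add.** A standardised risk difference adjusted for baseline EASI has variance of about (1 − R²) times the unadjusted variance. The document gives no association between baseline EASI and EASI50, so R² is an assumption and zero belongs in the range.

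- Standard error ratio = √(1 − R²)
- Unadjusted 95% half-width = 1.96·√(0.46/134) = 11.5 percentage points
- Equivalent extra patients = 268·[1/(1 − R²) − 1], on the 2·134 = 268 evaluable patients that carry the power
- Power = the formula in step 1 with 134/(1 − R²) per arm

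| Assumed R² | SE reduction | 95% half-width (points) | Equivalent extra patients | Power |
|---|---|---|---|---|
| 0 | 0% | 11.5 | 0 | 92.1% |
| 2% | 1.0% | 11.4 | 5 | 92.6% |
| 5% | 2.5% | 11.2 | 14 | 93.3% |
| 10% | 5.1% | 10.9 | 30 | 94.5% |

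**3. Check by simulation.** Trials of 134 per arm were generated from a logistic model with marginal risks of 50% and 30% and a standard normal baseline covariate, 1,500 per scenario. The odds ratios per SD are assumptions.

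| Odds ratio per SD | R² | Variance ratio, adjusted to unadjusted |
|---|---|---|
| 1.0 | 0 | 1.01 |
| 1.25 | 0.011 | 0.99 |
| 1.5 | 0.035 | 0.97 |
| 2.0 | 0.092 | 0.92 |
| 3.0 | 0.189 | 0.83 |

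The ratios follow 1 − R² closely. With a covariate that predicts nothing, there is no gain and almost no loss.

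**4. The named links with a covariate.** In 200 simulated trials per link and scenario, the default fit was counted as failed if it stopped with an error, did not converge, lacked finite standard errors or gave fitted risks outside 0 to 1.

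| Odds ratio per SD | Log link | Identity link |
|---|---|---|
| 1.5 | 16% | 19.5% |
| 2.0 | 72% | 75.5% |

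These rates depend on the assumed covariate distribution and on default fitting. They show that the problem can be common, not how often it would occur in this trial.

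**The case against.** The strongest case against has four parts.

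- **Silence is not exclusion.** The section never calls the primary model unadjusted, and a covariate list is commonly left to the analysis plan, which is announced but not shown. This stands. A reader might infer that the protocol rules out baseline EASI; it does not. What remains is that the links are already fixed here, and they suit adjustment badly.
- **There is no inconsistency with the longitudinal models.** Those model repeated scores, where baseline adjustment is routine. EASI50 is already measured against each patient's own baseline, so the same benefit cannot be assumed. The median split is exploratory and looks for effect modification; it does not show that the plan treats baseline EASI as prognostic. This also stands, and it is why the gain may be close to nil.
- **The unadjusted analysis is sound.** It is unbiased under randomisation, its interval already allows for chance imbalance, and it matches the sample size test. No stratification factor is named that would call for adjustment. All of this is correct.
- **The two complaints exclude each other.** With treatment alone the links do not fail; with covariates, the precision complaint falls away. This is fair as logic. The fitting problem is no defect of a treatment-only model, but it does mean that adjustment should come with a different estimator.

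**Conclusion.** The point holds as a low-priority efficiency improvement. As written, the primary model names no covariate, uses links that can break down with a continuous one, and leaves unused a baseline measurement that every patient has. For an assumed R² of 0 to 10%, adjustment would bring between nothing and about 2.4 points of power (92.1% to 94.5%), or between 0 and about 30 patients' worth of information on 268.

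A reader might go further and conclude that precision is certainly being lost at no cost, or that the primary estimate is left biased by imbalance in severity. The document supports neither. It reports no association between baseline EASI and EASI50, the gain requires a change of estimator, and the unadjusted estimate is unbiased.

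The result rests on the planning rates of 50% and 30%, on R² as an assumption, and on the natural but not explicit reading that the primary analysis is unadjusted. The unseen analysis plan may already deal with it.

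**What to change.** In the statistical analysis plan, before database lock, prespecify one logistic model for EASI50 at 3 months with arm and continuous baseline EASI. Centre may be added but is not essential. From it, report the standardised (marginal) risk difference and relative risk with robust or bootstrap 95% confidence intervals. These are the same two effect measures that the protocol promises, so the reported quantities do not change. Keep the unadjusted binomial GLM as a sensitivity analysis, which preserves the link to the sample size calculation.

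The cost is a few lines of analysis plan text and minor programming. No new data are needed for baseline EASI, and the sample size stays as it is. The downside is a small added complexity for a gain that may turn out close to nil.

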### Inclusion criteria

In order to be eligible to participate in this study, a subject must meet all of the following criteria:Adult (≥ 18 years of age) patient meeting the UK working party criteria for AE [17];AE insufficiently controlled by standard topical care and therefore eligible for OTT or NB-UVB;Validated Investigator Global Assessment for Atopic Dermatitis (vIGA-AD) of ≥ 2 (moderate disease);Eczema Area and Severity Index (EASI) of ≥ 7 (moderate disease); andAbility to provide written informed consent.

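### The exploratory severity subgroup splits baseline EASI at the sample median; a continuous interaction would usually tell more, at almost no cost

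*Protocol article*

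**What the plan says.** The section on statistical methods for primary and secondary outcomes introduces subgroup work in one sentence: "Exploratory subgroup analyses will be run, e.g., location of receiving NB-UVB" (clinic or home), and then a second example, patients "below or above the median EASI score at baseline". It mentions no interaction test, no fixed clinical cut-point and no analysis of EASI as a continuous modifier, but it excludes none of these. The section closes by deferring detail: "A detailed statistical analysis plan will be completed before the database lock".

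Elsewhere the protocol gives only the limits of the score. Entry requires an EASI of at least 7 (Inclusion criteria), and the scale runs to 72 (Primary outcome). No mean, standard deviation or shape is given for baseline EASI. The primary outcome is EASI50 at 3 months, a halving from baseline.

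**The concern.** A median split treats a patient just above the cut like one near the top of the scale, and treats two patients just either side of it as different. If benefit rises or falls gradually with severity, information is thrown away. The cut is also set by whoever happens to be recruited, so its value is unknown until baseline data are in.

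The outcome gives a further reason to expect a graded relation. EASI50 is relative to baseline: halving means 0.5 × 7 = 3.5 points for a patient at the entry floor, but 0.5 × 40 = 20 points for a patient at 40. A gradual dependence on baseline is at least as natural to examine as a jump at the sample median.

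At stake is how much an exploratory analysis can show about whether the effect varies with severity. The trial was sized for the main effect only.

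**Working it through.** **Inputs from the protocol.** Sample size section: 134 per arm, 90% power, 30% versus 50%, two-sided 5%, 15% drop-out, 316 in total. Baseline EASI lies between 7 and 72. Everything about its shape below is an assumption.

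**The plan's own figure.** The protocol gives no figure for the subgroup analysis, only for the main comparison: "Sample sizes of 134 in both arms achieve 90% power to detect a difference".
- Pooled-variance formula: (1.960 × √(2 × 0.4 × 0.6) + 1.282 × √(0.3 × 0.7 + 0.5 × 0.5))² / 0.20² = 124 per arm.
- With a continuity correction this becomes 134, as stated. Without the correction, 134 per arm has 92.1% power.
- Drop-out: 2 × 134 = 268, and 268 / 0.85 = 315.3, so 316, as stated.

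The figures reproduce, and 268 evaluable patients is used below.

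**Information kept by a median split.** Suppose the treatment effect changes linearly with X. For small effects, the efficiency of the split relative to linear X is the squared correlation between X and the indicator that X exceeds its median:

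r² = (δ/2)² / Var(X), where δ = E[X | above median] − E[X | below median].

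A shift of origin, such as starting at 7, does not change r². The loss is 1 − r².

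| Assumed baseline shape | r² | Loss |
|---|---|---|
| Uniform | (1/4)² / (1/12) = 0.75 | 25% |
| Normal | 2/π = 0.637 | 36% |
| Gamma, shape 2, above 7 (simulated) | 0.553 | 45% |
| Exponential above 7 | (ln 2)² = 0.480 | 52% |
| Lognormal, log-SD 0.5 | 0.516 | 48% |
| Lognormal, log-SD 0.7 | 0.421 | 58% |
| Lognormal, log-SD 0.8 | 0.370 | 63% |

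For the lognormal, r² = (2Φ(s) − 1)² / (exp(s²) − 1). At s = 0.7 this is 0.516² / 0.632 = 0.421.

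**Shapes confined to EASI 7 to 72.** Seven lognormals (median 10 to 16, log-SD 0.5 to 0.8 before truncation) were cut to 7–72 and simulated. The loss is 46% to 54% if modification is linear in raw EASI, and 31% to 34% if it is linear in log EASI. The log-scale range is the one to compare with a log-transformed interaction.

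**In patients.** A 36% loss is like having 268 × 0.637 = 171 patients for the interaction. At 25% it is 268 × 0.75 = 201, and at 63% it is 268 × 0.37 = 99. On the log scale it is 268 × 0.69 = 185 down to 268 × 0.66 = 177.

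**Power of an interaction test.** This was a logistic simulation with 268 patients and 2,500 repeats per setting. The control risk was 30% throughout, and the treated risk was centred at 50% on the log-odds scale. The effect varied by 0.8 log-odds per SD of baseline EASI (linear truth), or by 0.8 log-odds up or down either side of the median (step truth).

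| Baseline shape | Linear truth: continuous / split | Step truth: continuous / split |
|---|---|---|
| Normal | 83% / 65% | 71% / 84% |
| Exponential above 7 | 78% / 48% | 61% / 83% |
| Lognormal truncated to 7–72 | 79% / 49% | 61% / 82% |

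At 0.5 log-odds per SD and a normal baseline, the linear-truth figures are 46% and 31%, and the step-truth figures are 33% and 44%. With no interaction, all tests rejected in 4% to 6% of repeats. The continuous form wins when the truth is smooth, and the split wins when the truth is a step at the median.

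**The case against.** The strongest reply is that the protocol commits to very little here. The split is one of two examples in an exploratory sentence, no interaction test is planned, and how a modifier is modelled is ordinarily settled in the analysis plan, which is not shown and may already include a continuous analysis. Continuous EASI is recorded for every patient, so nothing is lost for good. A median split also gives balanced groups and a simple table. All of that stands, and it keeps the point minor. It does not remove it, because the article names a specific method rather than staying silent.

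A second reply is that no single percentage can be given. That also stands. A reader might infer that the split discards some fixed share of this trial's information, say 36% to 58%. The protocol does not support this: that range needs a normal to moderately skewed baseline and an effect linear in raw EASI, and neither is stated.

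A reader might also infer that the choice impairs a decision on which severity groups keep access to NB-UVB, or a planned pooling of severity subgroups. The Background and Discussion ask whether NB-UVB has a place in the treatment algorithm, and foresee pooling of the evidence with other studies. Neither raises a severity-specific access question or subgroup pooling, and the Data Availability section offers the data on request.

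**Conclusion.** The point holds as a cheap improvement to an exploratory analysis. If benefit varies smoothly with severity, the median split loses information relative to continuous EASI: about 36% under normality, about 25% to 63% over the other shapes tried, and about 31% to 34% if modification is linear in log EASI. These figures rest on an assumed baseline distribution and an assumed form of modification, and the range is not a bound; a heavier-tailed lognormal would lose more. Under a true step at the median the split loses nothing and has more power.

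The primary analysis, its sample size and the main conclusion do not depend on this choice.

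**What to change.** In the statistical analysis plan, before database lock, add a sentence to the exploratory subgroup section: the interaction of arm with baseline EASI will be estimated with EASI as a continuous variable in one prespecified form (for example log-transformed), with a restricted cubic spline as a check on that form. Show the estimated risk difference, with its confidence band, across the observed range of EASI, and keep the below/above-median table for display. Name the effect scale, since an interaction depends on it.

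Cost: no new data, no added patients and no change to the primary analysis. The presentation is slightly less simple, the main form carries an assumption about shape, and a spline spends extra degrees of freedom on an interaction the trial was not sized to detect.

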### Interventions

We will investigate a course of NB-UVB + OTT (home or out-patient) of 12 weeks (range of at least 8 weeks and up to 16 weeks) compared to OTT alone. In the interventional arm, NB-UVB will be given 3 times per week with daily OTT. In the control group daily OTT will be applied.

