#### Participant timeline

After screening and informed consent, participants will be randomized in the NB-UVB + OTT or OTT group. Study participation will entail 6 study visits. The baseline visit will take place before therapy starts. The follow-up visits are at 4 weeks, 3, 6, 9, and 12 months. Visits may be rescheduled within 1 month of the initial planning. Extra visit(s) will take place in case of therapy switch or stop. Patients in the NB-UVB + OTT group will undergo phototherapy 3 times a week for a planned period of 12 weeks from baseline, with a possible range of 8 to 16 weeks, depending on therapy response. Therapy duration will be determined in accordance to standard clinical practice. NB-UVB can be applied in the outpatient clinic or at home. Participants in both groups will apply daily OTT for a minimum of 3 months. Patients will be asked to keep all tubes of used OTT (excluding emollients) and bring them to the study visits. During the visits, data about NB-UVB and OTT will be collected. Patients will be asked for possible SAEs and AEoSIs with details such as start and stop date, intensity/severity of adverse events, probability of relation with NB-UVB + OTT or OTT, whether the allocated therapy was interrupted, and co-medications. During all visits, a physical examination by a blinded outcome assessor will take place to assess disease severity. Additionally, a set of questionnaires will be sent to the patient. The questions can be filled out on an electronic device, either at home or during the study visit in the outpatient clinic. At baseline, 3 months, and 12 months, an additional set of questionnaires regarding disease burden on productivity and medical costs will be filled out (Fig. 1). Subjects that have completed trial participation or have discontinued prematurely will be referred back to standard eczema care.

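### The cost-utility analysis is called societal, but its cost list names no patient or family costs; applied as written, it omits travel and time for NB-UVB sessions and would tilt cost per QALY towards NB-UVB

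*Protocol article*

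**What the plan says.** In the protocol article, under Statistical methods for primary and secondary outcomes, the economic evaluation is a "cost-utility analysis (CUA) from a societal perspective with the costs per quality-adjusted life year (QALY) as a primary outcome". The same paragraph then itemises the costs. The first group opens with "The analysis will include the costs of health care (in-patient and out-patient hospital care, institutional care elsewhere" and goes on to care outside hospital and extramural drugs. The second group is "costs of productivity loss resulting from sick leave from work or lowered efficiency while at work". There is no third group. Resource volumes are to come from case report forms and "patient questionnaires on medical consumption (iMCQ) and productivity loss (iPCQ) adapted for this study"; the adaptations are not described.

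The section Interventions states that "NB-UVB will be given 3 times per week with daily OTT", for a course "of 12 weeks (range of at least 8 weeks and up to 16 weeks) compared to OTT alone". Participant timeline repeats that these patients "will undergo phototherapy 3 times a week for a planned period of 12 weeks from baseline", and allows treatment in the clinic or at home without giving the split. The section OTT bars control patients from an NB-UVB course during follow-up. Both arms have the same six study visits.

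**The concern.** A patient's travel to a phototherapy session is neither health care nor lost productivity. The same holds for time spent being treated, unless it is taken as sick leave. The declared perspective is therefore wider than the costs listed under it.

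In many trials this would matter little, because patient costs roughly balance between arms. Here the sessions belong to one arm only. Leaving out a cost tied to them makes the incremental cost of NB-UVB too low. Reimbursement of NB-UVB is a stated motive for the trial (Background and rationale; Discussion), so cost per QALY is likely to be read closely by payers. Travel arises only for clinic sessions, so any cost comparison of clinic with home treatment would also be distorted.

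**Working it through.** The article states no cost and no cost per QALY, so there is no figure of its own to reproduce. The check has four steps.

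**1. Number of sessions.** Inputs: three per week; 8, 12 (planned) or 16 weeks (Interventions; Participant timeline).
- 3 × 8 = 24
- 3 × 12 = 36
- 3 × 16 = 48
- OTT arm: 0

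These are clinic journeys only if every session is in the clinic. Home sessions take time but need no journey.

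**2. Direction.** Let S be the number of sessions, c the clinic share, k₁ the patient cost of a clinic session (travel plus time), k₂ that of a home session (time only), and F the excess of other omitted patient costs in the OTT arm over the NB-UVB arm, for example travel for later systemic treatment.

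Omitted incremental cost = S × [c × k₁ + (1 − c) × k₂] − F

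Shift in cost per QALY = omitted incremental cost ÷ QALY gain

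With a positive QALY gain, the shift favours NB-UVB unless F exceeds the session term.

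**3. Illustrative size, F set to 0.** None of these inputs is in the document. Assumed: k₁ = EUR 5-30, k₂ = EUR 2-10, QALY gain 0.02, S = 36.

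| Clinic share | Omitted cost per NB-UVB patient | Shift per QALY |
|---|---|---|
| 1 | 36 × 5 to 36 × 30 = EUR 180-1,080 | EUR 9,000-54,000 |
| 0.5 | 36 × 3.5 to 36 × 20 = EUR 126-720 | EUR 6,300-36,000 |
| 0 | 36 × 2 to 36 × 10 = EUR 72-360 | EUR 3,600-18,000 |

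The result depends heavily on the assumptions. At half clinic, a QALY gain of 0.01 gives EUR 12,600-72,000 and one of 0.05 gives EUR 2,520-14,400. With a higher assumed cost of EUR 17-90 per clinic session (EUR 2-10 travel plus 1-2 hours at EUR 15-40), 36 clinic sessions come to 36 × 17 to 36 × 90 = EUR 612-3,240, so the upper end is three times the 1,080 above.

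**4. How large an offset would cancel the travel part?** At equal travel cost per journey, OTT patients would have to make 36 × c more care journeys on average than NB-UVB patients: 36 if all sessions are in the clinic, 18 if half are, 0 if none are. An offset of that size looks unlikely where clinic treatment is common. Where nearly all treatment is at home, the travel part could cancel or even reverse.

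**The case against.** The strongest reply is that the omission from the actual analysis is not proven. The article says what the analysis will include, not that nothing else will be. The two questionnaires are adapted in ways not described, and they sit in an additional file that is not shown. A detailed analysis plan is also promised before database lock. This stands as a limit on how firmly the point can be put. It does not remove the point: the article did not leave cost categories to another document but listed them with sub-items, and the list does not match the perspective named in the same paragraph.

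A reader might infer that cost per QALY is shown to be too favourable, or that every NB-UVB patient has 24 to 48 unpaid-for journeys. The document supports neither. The bias is conditional on the list being applied as written and on a positive QALY gain. Home treatment needs no session travel, and its share is unknown.

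Two further objections hold. Both arms may move to systemic therapy after 3 months (sections NB-UVB and OTT), and travel for that care falls outside the list too; if OTT fails more often, part of the difference is offset. Work hours lost to sessions may already be reported in the iPCQ, so adding them by session count could count them twice. Finally, whether to value unpaid time at all is a convention that the document does not settle.

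**Conclusion.** The point holds in a conditional form. The declared societal perspective and the itemised costs do not agree. Followed as written, the list omits travel to clinic NB-UVB sessions and time spent on clinic or home sessions, a burden of up to 24 to 48 sessions in one arm and none in the other. Given a positive QALY gain and no larger offset from later care, cost per QALY would be biased towards NB-UVB, mainly for clinic-treated patients.

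The session counts rest on the document. The euro figures do not: unit costs, clinic share, QALY gain and offset are all assumed, and the ranges show only that the shift need not be trivial. None of them should be quoted as an estimate of the bias. The economic evaluation is affected; the EASI50 comparison is not. The change should be made before the analysis plan is final.

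**What to change.** Add patient travel to the cost list, valued as recorded clinic sessions and other care visits **in both arms** times a unit cost. Show time spent on clinic and home sessions as a sensitivity analysis, excluding hours already reported in the iPCQ. Report cost per QALY with and without these costs. If the adapted questionnaires already cover them, one sentence saying so is enough. If they will not be included, rename the perspective as health care plus productivity.

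The cost is small. NB-UVB data are already gathered at visits (Participant timeline), though the plan should confirm that session counts by location are among them. What is added is a little analysis work, unit-cost assumptions to be stated, and a cost per QALY that may turn out less favourable to NB-UVB.
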